## Abstract

**Introduction:**

Atherosclerotic cardiovascular disease (ASCVD) continues to be a leading cause of preventable death globally. Polygenic risk scores (PRS) offer a way to detect individuals at higher relative risk of developing ASCVD, but they have not yet been incorporated into routine clinical practice. Pragmatic trials offer a way to evaluate the integration of PRS into cardiovascular disease prevention in primary care, allowing for a more accurate assessment of their effectiveness in everyday clinical practice.

**Methods and analysis:**

This trial evaluates the effectiveness of preventive statin treatment on reducing the incidence of cardiovascular events and death over 5 years in women (aged 55–80) and men (aged 45–80) with a high coronary artery disease PRS. This is a pragmatic, multicentre, open-label, parallel group, randomised clinical trial with a 1:1 allocation ratio to intervention (n=1350), receiving preventive rosuvastatin 20 mg treatment or control (n=1350), receiving current standard of care. Following the intention-to-treat principle, all randomised participants are analysed according to their allocated group, with the primary outcome defined as time to first major adverse cardiovascular event, comprising ischaemic heart disease, stroke or transient ischaemia, peripheral vascular occlusion and stenosis, revascularisation or cardiovascular death.

**Ethics and dissemination:**

This trial has received ethical approval from the Estonian Committee on Bioethics and Human Research (13.06.2024 nr 1.1-12/1531) and the Estonian Ethics Committee for Medicinal Products (19.12.2024 nr RKU-4/92).

**Trial registration number:**

NCT06820086.

STRENGTHS AND LIMITATIONS OF THIS STUDYPragmatic, multicentre, open-label, parallel-group randomised design with 5-year follow-up and primary endpoint ascertainment through national health registries.Embedded recruitment within the Estonian Biobank cohort enables nested pharmacogenetic and microbiome sub-studies using pre-existing genetic data and biospecimens.Contamination risk due to disclosure of high coronary artery disease polygenic risk scores (PRS) to control arm participants at enrolment, which may prompt independent risk-seeking behaviour despite physician blinding.The generalisability of findings to younger high-PRS individuals may be limited given the necessarily older study population required to observe sufficient cardiovascular events.

## Background and rationale

 Atherosclerotic cardiovascular disease (ASCVD) is a significant cause of preventable death worldwide.^1^ Incorporating polygenic risk prediction into the clinical management of ASCVD holds particular importance because of the genetic characteristics of the disease.^2^,^4^

Polygenic risk scores (PRS) are important determinants currently not implemented in the standard clinical risk assessment of cardiovascular disease (CVD).^5^ Studies show that healthy individuals with a very high PRS have a similarly high clinical risk for CVD, as do those with high-impact genetic variants such as those for familial hypercholesterolaemia.^6^,^8^ As genetic testing is not regularly conducted to assess coronary artery disease PRS (CAD PRS), we tend to miss the window of CVD primary prevention among those individuals.^9^

A few focused clinical studies have examined patient responses to CAD PRS communication, finding that genetic risk disclosure alone has not meaningfully changed health behaviour.^10^,^12^ As the atherosclerotic processes develop faster among high-PRS individuals, a more feasible approach could involve combining behavioural interventions with early-onset preventive lipid-lowering treatment with statins.^13 14^

Low-density lipoproteins (LDLs) contribute to ASCVD, and their management with lipid-lowering medications is essential.^15^ Recent studies have found that high PRS amplifies the cardiovascular impact of LDL-C, such that individuals with high PRS and only moderately elevated LDL-C may exceed the treatment threshold for lipid-lowering therapy.^16 17^ Lipid-lowering therapy such as statin treatment has proven to be particularly effective in lowering the LDL of patients with high polygenic risk.^14 18^ Still, the implementation of statin treatment can be challenging as the prescription rate of statins for primary prevention of ASCVD remains low at the primary care level.^19 20^ Significant disparities in controlling LDL cholesterol (LDL-C) levels are evident throughout Europe, with only 20% of patients at high and very high risk reaching the LDL-C goals recommended by the 2019 European Society of Cardiology (ESC).^21 22^ The inadequate prescription of statins is attributed to physicians underestimating the CVD risk in patients and not staying current with the guidelines outlined by the ESC for the prevention and treatment of CVD.^23^

Current research lacks sufficient indication-specific and prospective studies on the utility of PRS for CVD prevention in real-life settings. Our trial seeks to address this knowledge gap by conducting a pragmatic trial where preventive statin therapy is prescribed to individuals with high CAD PRS, aiming to reduce the occurrence of CVD and cardiovascular death.

### Objectives

The primary objective of the EE-PRS trial is to assess the effectiveness of preventive statin treatment based on a high CAD PRS on reducing the incidence of cardiovascular events and death over 5 years in women (aged 55–80) and men (aged 45–80).

Secondary objectives include assessment of all-cause mortality, cardiovascular risk factor modification and treatment adherence and acceptability. The trial also includes pharmacogenetic and microbiome substudies and a cost–utility analysis of PRS-guided statin therapy compared with standard care.

## Methods

### Trial design

This is a pragmatic, multicentre, open-label, parallel group, randomised clinical trial with a 1:1 allocation ratio to intervention (n=1350), receiving preventive rosuvastatin 20 mg treatment or control (n=1350), receiving current standard of care.

### Trial setting

This clinical trial adopts a pragmatic approach as it aims to evaluate the real-world effectiveness of polygenic risk-based preventive statin therapy within Estonia’s primary care system. Conducted over 5 years across approximately 300 primary care practices, the trial leverages Estonia’s unique healthcare infrastructure, which includes a robust primary care network and the Estonian Biobank (EstBB) with genetic data from over 200 000 individuals, from which eligible participants are identified and recruited.

Enrolled participants will receive all trial interventions at their own primary care practice. Intervention arm participants may collect their statin prescription at any pharmacy in Estonia, while control arm participants continue to receive standard primary care without the use of a placebo. Estonia’s small size and centralised healthcare system make it an ideal setting for such a trial, enabling efficient implementation and monitoring.

### Eligibility criteria

This trial intervention is aimed at individuals with high (top 20%) CAD PRS, men aged 45–80 years and women aged 55–80 years. Inclusion and exclusion criteria are listed in box 1.

Box 1Inclusion and exclusion criteria.Inclusion criteriaMen aged 45–80 on 1 January 2025.Women aged 55–80 on 1 January 2025.CAD PRS top 20% confirmed by the Estonian Biobank.The family physician of the study participant has been contracted to participate in the trial.Written informed consent has been provided to participate in the trial.Exclusion criteriaDiagnosed with ischaemic heart disease (I20–I25), stroke or transient ischaemia (I60–64, I69, G45), peripheral vascular occlusion (I65–66, I67.2, I70, I73.9), diseases of liver (K70–K77), end-stage renal disease (N18.0), mental and behavioural disorders due to psychoactive substance use (F10–F19).Currently using statin treatment or has been prescribed statins in the past 3 years.Has a confirmed pathogenic variant associated with familial hypercholesterolaemia (APOB, PCSK9, LDLR genes) as verified by the EstBB.Is currently participating in other clinical trials.Comorbid physical or mental illnesses that prevent the individual from granting consent or participating in the trial (according to the judgement of the investigator).Individuals taking:a combination of sofosbuvir/velpatasvir/voxilaprevir (used to treat hepatitis C);ciclosporin;fusidic acid orally or by injection.Individuals with hypersensitivity to the active substance (rosuvastatin or atorvastatin) or its excipients.

### Intervention and comparator

The comparison between the statin treatment arm (intervention) and control group (comparator) is conducted pragmatically within the primary care setting, with no placebo used in the control arm. This design ensures that control participants continue to receive usual care from their family physician while intervention arm participants receive preventive statin therapy on top of standard care. This approach reflects real-world clinical practice and allows for a direct assessment of the added value of integrating PRS-guided statin therapy into routine CVD prevention.

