### Intervention arm

The first study visit begins with the family physician explaining the nature of polygenic risk and responding to the participant’s questions. The physician will then proceed to counselling the patient in relation to improving their health behaviours utilising techniques such as motivational interviewing. During the visit, the physician will take baseline measurements and blood analyses of the participant and prescribe statin treatment (rosuvastatin 20 mg, 1 tablet per day), explaining treatment schemes and potential side effects. Intervention arm participants attend next primary care visits at months 3, 12 and 60, at which physical measurements, blood tests and side effect assessments are performed by the family physician.

Between scheduled primary care visits, study nurses conduct telemedicine visits at months 6, 24, 36 and 48 to support participant retention throughout the trial. They are also responsible for monitoring trial medication adherence by tracking statin procurement from pharmacies via a dedicated database and contacting the physician or participant as needed if discrepancies in prescribing or dispensing are identified.

The trial intervention is a fixed-dose statin strategy (rosuvastatin 20 mg once daily). Treatment is not titrated to LDL-C targets, as the trial evaluates the effect of PRS-guided statin initiation and sustained exposure on cardiovascular events rather than the effect of intensified lipid lowering. Where rosuvastatin 20 mg is not tolerated, the predefined adverse reaction algorithm applies. Family physicians retain clinical discretion to manage non-trial cardiovascular risk factors according to current guidelines.

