### Control arm

Family physicians of the control arm participants will not be informed of their patients’ participation in the trial until the last visit at month 60. This helps to ensure that the care provided to the control group participants reflects as much as possible real-life primary care practice.

The control arm baseline measurements and blood samples are taken at partner hospitals and laboratories across Estonia, all blood analyses are done centrally at the Tartu University Hospital medical laboratory. Physicians are blinded to the results of baseline control arm measurements and analyses until the end of the trial. At month 60 of the trial, physicians will be informed about their patients who were in the control arm for scheduling a final study visit. During the final trial visit, the physicians will inform participants of their CAD PRS, provide counselling and take final measurements.

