Despite its strengths, this study has potential limitations, including the open-label design, which may introduce potential biases in outcome reporting.^32^ The absence of a placebo control is a deliberate trade-off inherent to the pragmatic design: a placebo-controlled trial would substantially reduce real-world generalisability and increase trial complexity and cost, while not resolving the central question of whether PRS-guided prescribing improves outcomes in routine care. A placebo-controlled design would also not preserve effective blinding in this trial, as the rapid and substantial reduction in LDL-C produced by statin therapy would diverge from placebo within months of randomisation and be apparent through routine lipid monitoring. Although control-arm physicians are not informed of their patients’ trial participation until the end of the study period, there is a risk of contamination, as all participants are informed about their high PRS during the consenting process. This awareness may influence their health behaviours or lead them to seek risk mitigation strategies independently. To quantify potential contamination, statin prescription and dispensing data from the Estonian national prescription database will be analysed for both arms. The generalisability may be limited, as we include participants from the EstBB cohort, which predominantly consists of more educated individuals with relatively high socioeconomic status.^25^

As this study focuses on clinical outcomes and aims to assess differences in major cardiovascular events over a relatively short period, we must select a middle-aged and older population where cardiovascular events are more likely to occur within the study timeframe. This limits the generalisability of findings to younger individuals, who may stand to benefit most from early PRS awareness through timely lifestyle modification and preventive intervention to reduce lifetime cardiovascular risk.^33^ Although concerns around adherence, drug interactions and quality of life have contributed to statin underuse in individuals aged 75 and older, emerging evidence from real-world studies and large ongoing trials increasingly supports their benefit for primary prevention in this population.^34^,^37^

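### The stated contrast is statin added to standard care, but the intervention arm also gets counselling, visits and nurse contacts, so the result belongs to a programme, not to the statin alone

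*Protocol article*

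**What the plan says.** The primary objective is to "assess the effectiveness of preventive statin treatment based on a high CAD PRS". The Intervention and comparator section describes the contrast in the same terms: "intervention arm participants receive preventive statin therapy on top of standard care", while controls have usual care, and this "allows for a direct assessment of the added value of integrating PRS-guided statin therapy into routine CVD prevention". The Intervention arm section calls the intervention a fixed-dose statin strategy, and the sample size section ascribes the anticipated 30% hazard reduction to statin treatment.

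The Intervention arm section then lists what else that arm receives. The first visit opens with the family physician explaining polygenic risk, and continues: "The physician will then proceed to counselling the patient in relation to improving their health behaviours utilising techniques such as motivational interviewing". Physician visits follow at months 3, 12 and 60, and study nurses hold telemedicine visits at months 6, 24, 36 and 48.

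For controls, the Control arm section describes baseline measurements away from the family practice, a physician who does not know of the participation, and one final physician visit at month 60: "During the final trial visit, the physicians will inform participants of their CAD PRS, provide counselling and take final measurements". Elsewhere the article says that "all participants are informed about their high PRS during the consenting process" (Discussion), and its list of strengths and limitations refers to "disclosure of high coronary artery disease polygenic risk scores (PRS) to control arm participants at enrolment".

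**The concern.** If two arms differ by a drug and by a counselling and contact package, the hazard ratio estimates the joint effect. The protocol's wording assigns it to the statin. A trial report that follows that wording would credit the statin with whatever the counselling and extra contact add.

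The document itself leaves room for such an effect. The Background favours combining behavioural interventions with statin treatment, and Table 1 compares blood pressure, BMI, waist circumference, smoking and alcohol use between arms as effects of the trial interventions. These are natural targets of health-behaviour counselling.

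The comparator also needs a clear description. The Background says that PRS is not part of standard risk assessment. If controls learn of their high PRS at consent, they have usual care with knowledge of their PRS. If they learn of it only at month 60, disclosure is one more component given to the intervention arm alone.

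**Working it through.** **Step 1. The arms side by side, from the Intervention arm and Control arm sections.**

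| Component | Intervention | Control |
|---|---|---|
| Statin prescribed by the trial | Yes | No |
| Physician explains polygenic risk | First visit | Month 60 |
| Behavioural counselling | First visit, motivational interviewing | Month 60 |
| Follow-up physician visits | Months 3, 12, 60 | Month 60 |
| Nurse telemedicine visits | Months 6, 24, 36, 48 | None described |
| Baseline results | Obtained by the family physician | Withheld from the family physician until the end |

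The excess before month 60 is therefore the first consultation with explanation and counselling, two follow-up physician visits (months 3 and 12) and four nurse contacts. Month 60 occurs in both arms and is not part of the excess.

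**Step 2. What the article acknowledges.** The strengths and limitations list, the Blinding section and the Discussion cover controls acting on their PRS. The Adherence section tracks statin procurement by controls. No passage names the counselling and contact imbalance as a limit on attribution.

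**Step 3. Illustration of size.** The only input from the document is a hazard ratio of 0.70, from the 30% reduction in the sample size section. The other inputs are assumptions: a package hazard ratio b between 1 and 0.90, and a share c of controls, from 0 to 30%, who take a statin from the start with full effect.

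Share of the log hazard ratio due to the package, taking c = 0:
- b = 0.95: ln(0.95)/ln(0.70) = 14%
- b = 0.90: ln(0.90)/ln(0.70) = 30%

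With statin-only hazard ratio s, the arm-level hazard ratio is approximately s·b / [(1−c) + c·s]. Setting this to 0.70 and solving gives s = 0.70(1−c) / (b − 0.70c):
- b = 1, c = 0: s = 0.70
- b = 0.90, c = 0: 0.70/0.90 = 0.78
- b = 1, c = 0.30: 0.49/0.79 = 0.62
- b = 0.90, c = 0.30: 0.49/0.69 = 0.71

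A package benefit makes the observed ratio look better than the statin alone, and statin use by controls makes it look worse. With both present they can nearly cancel, as the last line shows. The document gives neither b nor c, so the net direction is unknown.

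**Step 4. Sample size.** The target of 2700 is not at issue. It came from simulation and the article gives no event rate, so it can be neither reproduced nor refuted here, and the point does not rest on it.

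**Step 5. Timing of disclosure.** On their face, the month-60 sentence in the Control arm section and the consent or enrolment statements in the Discussion and the strengths and limitations list do not agree. They can be squared if the month-60 visit is a physician's explanation of a result already known, but the text does not say so.

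**The case against.** This is a pragmatic trial, and bundling is legitimate in one. Counselling at a prescribing visit can be read as part of PRS-guided statin care, and Table 1 speaks of a primary prevention programme. The nurse contacts serve retention and statin adherence, so much of their effect would run through the statin. Disclosure to controls is acknowledged and their statin use is tracked. All of this stands, and it limits the point. It does not remove it: the objective, the comparator section and the sample size section still name only the statin, and the behavioural counselling is not a means of delivering it.

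A reader might go further and infer three things that the documents do not support.
- That a positive result could not be ascribed to the statin at all. Under the assumed package effects above, 70% to 86% of the log hazard ratio would remain with the statin, and those package effects have no source in the document.
- That the article claims to isolate the value of telling people their PRS. Its claim concerns PRS-guided statin therapy.
- That the disclosure passages are irreconcilable. A later physician explanation is a plausible reading of the month-60 sentence.

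**Conclusion.** The point holds as one of attribution and wording. The randomised comparison is internally valid for what is delivered: statin, explanation of risk, counselling and follow-up against usual care. It does not support a claim about the statin alone, and the limitations do not say so. The range of 0.62 to 0.78 around an observed 0.70 rests wholly on assumed package effects of up to 10% and assumed statin use by controls of up to 30%. It shows the order of magnitude and is not an estimate of bias. The timing of disclosure to controls must be settled, because it decides whether knowledge of the PRS is common to both arms or part of the tested bundle. Nothing here calls for a change to randomisation, sample size or treatment.

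**What to change.** - Restate the primary objective, the two sentences in the Intervention and comparator section (statin added to standard care; direct assessment of added value) and the planned conclusion as the effect of a PRS-guided programme of statin plus counselling and follow-up, against usual care, in high-PRS adults.
- Add the counselling and contact imbalance to the limitations as a limit on attribution to the statin.
- Reconcile the Control arm section with the Discussion and the strengths and limitations list on when and how controls learn their PRS, and describe the comparator accordingly.
- Use the end-of-trial arm differences in blood pressure, BMI, waist circumference, smoking and alcohol use, already planned in Table 1, together with the tracked statin use in controls, as supportive evidence on non-statin effects. They can indicate whether such effects are likely, but cannot divide the hazard ratio into parts.

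The cost is wording, since the data are already to be collected. The downside is a narrower headline claim.

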### Intervention arm

The first study visit begins with the family physician explaining the nature of polygenic risk and responding to the participant’s questions. The physician will then proceed to counselling the patient in relation to improving their health behaviours utilising techniques such as motivational interviewing. During the visit, the physician will take baseline measurements and blood analyses of the participant and prescribe statin treatment (rosuvastatin 20 mg, 1 tablet per day), explaining treatment schemes and potential side effects. Intervention arm participants attend next primary care visits at months 3, 12 and 60, at which physical measurements, blood tests and side effect assessments are performed by the family physician.

Between scheduled primary care visits, study nurses conduct telemedicine visits at months 6, 24, 36 and 48 to support participant retention throughout the trial. They are also responsible for monitoring trial medication adherence by tracking statin procurement from pharmacies via a dedicated database and contacting the physician or participant as needed if discrepancies in prescribing or dispensing are identified.

The trial intervention is a fixed-dose statin strategy (rosuvastatin 20 mg once daily). Treatment is not titrated to LDL-C targets, as the trial evaluates the effect of PRS-guided statin initiation and sustained exposure on cardiovascular events rather than the effect of intensified lipid lowering. Where rosuvastatin 20 mg is not tolerated, the predefined adverse reaction algorithm applies. Family physicians retain clinical discretion to manage non-trial cardiovascular risk factors according to current guidelines.

